#### Post-procedural management

Following completion of the procedure, participants will be taken to the post-procedure recovery unit. Any complications related to the procedure will be recorded and managed if required. Participants will be discharged from the unit as per routine hospital policy. As per standard of care, participants will be advised to take one to two tablets of Percocet (containing 5 mg of oxycodone and 325 mg of acetaminophen) or Tylenol number 3 (containing 30 mg of codeine and 325 mg of acetaminophen) every 6 h if required to a maximum of 8 tablets in 24 h if they have pain intensity NRS scores higher than 3 out of 10. Frequency of use of these medications by study participants will be recorded and the average daily opioid consumption in oral morphine equivalents for the 1 week preceding the follow-ups at 1, 3, 6, and 12 months will be recorded.

In the event a subject is randomized but does not receive the trial interventions, the treatment will not be reassigned. Trial personnel will assess the patient and collect data throughout their enrollment in the trial. Participants in both arms will wear an actigraphy device (Appendix 1) to assess the quality and duration of sleep and activity for 1 week prior to the trial treatments (for collection of baseline data) and starting on the day of intervention for 1 month after to longitudinally assess the impact of the trial treatments on sleep and physical activity.

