#### Concomitant care

There will be no restrictions or changes to the baseline home medications, but study participants will be advised to avoid introduction of new analgesic agents in the post-treatment period.

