### Blinding

#### Blinding mechanism

Participants, physicians, and all outcome assessors will all be blinded during the conduct of the trial and statistical analysis. Assessors will remain blinded to their group assignments throughout the study. A Staff Pain Medicine physician with at least 5 years of experience in performing RFN of the CMBN and who is not involved in the assessment of outcomes will receive the randomization assignment and perform the procedure using the assigned technique. Biostatisticians who will analyze the data will be blinded to group allocation and the two study groups will be represented as I and II on the study database with no other identifiers.

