### Statistical methods

A statistician will be consulted to assist in data analysis and interpretation. Descriptive information for the sample’s study measures will include frequency distributions or proportions for categorical variables and means (standard deviations) or medians (interquartile ranges) (if non-normally distributed) for the continuous variables. To compare data between the two groups, categorical outcomes will be analyzed with the chi-square test and continuous variables will be analyzed with independent *t*-tests (or Wilcoxon rank sum test, as appropriate). A two-sided *p*-value of < 0.05 will be considered statistically significant. Both intention-to-treat (based on study arm allocation) and per-protocol (based on the participants who adhered to the study protocol and provided data at study outcome time points) analysis will be performed and reported.

Correlation between reduction in pain and improvement in function will be evaluated with a longitudinal model of changes from baseline to 3-month, 6-month, and 12-month follow-ups. An intention-to-treat strategy will be used for all analyses. Differences in treatment effects and 95% confidence intervals for pain and secondary outcome scores will be calculated using chi-square and odds ratios for dichotomous variables, and ANOVA (with *t*-tests for pairwise comparisons) and Mann–Whitney for continuous variables, as indicated. A set of logistic regression models for categorical outcome at 3 months will be created using variables hypothesized to have an effect on treatment (gender, intensity of pain, nature of injury), as well as those found to have a *p*-value less than 0.20 in univariate analysis. A secondary analyses based on data from participants who undergo unilateral versus bilateral RFN with each of the two study treatments is also planned. Missing data will be imputed using the “last observation carried forward” approach if at least 80% of the outcome data is available for the participant. All analyses will be performed using the SPSS program.

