### Criteria for subject withdrawal

Subjects have the right to withdraw from the study at any time, without providing a reason. In the event that a subject decides to prematurely discontinue the study, he/she will be asked if he/she can still be contacted for further information. This will be documented accordingly. If the subject has already received the study drug prior to withdrawal, the subject will be requested to be contacted for a safety follow-up visit.

When applicable, subjects should be informed of circumstances under which their participation may be terminated by the Investigator without their consent. The Investigator may withdraw subjects from the study in the event of intercurrent illness, adverse events, lack of compliance with the study or study procedures, any other reasons where the Investigator feels it is in the best interest of the subject, or at the request of the Research Ethics Board (REB). The reasons for withdrawal by the Investigator will be documented and explained to the subject. Should a subject decide to withdraw, all efforts should be made to complete and report the observations, particularly the follow-up questionnaires (if agreed to by the subject), as thoroughly as possible. If the reason for the removal of a subject from the study is an adverse event, the principal specific event will be recorded in the case report form. The subject will be followed until the adverse event is resolved if agreed by the subject.

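### The plan promises both ITT and per-protocol analyses, then says ITT is used for all analyses; neither set is tied to the non-inferiority claim, and the per-protocol rule is loosely worded

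*Protocol article*

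**What the plan says.** All the analysis-set wording is in the Statistical methods section of the protocol article.

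- The first paragraph opens the commitment with "Both intention-to-treat (based on study arm allocation) and per-protocol" and completes it with the definition "per-protocol (based on the participants who adhered to the study protocol and provided data at study outcome time points) analysis will be performed and reported".
- The second paragraph states "An intention-to-treat strategy will be used for all analyses". That sentence follows one on correlating pain reduction with function. It comes directly before the sentence on treatment differences and 95% confidence intervals for pain and secondary scores.

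Other sections bear on what adherence might mean.

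- Blinding mechanism: the operator is to "receive the randomization assignment and perform the procedure using the assigned technique".
- Post-procedural management: "In the event a subject is randomized but does not receive the trial interventions, the treatment will not be reassigned". Data collection continues for such a participant.
- Concomitant care: "study participants will be advised to avoid introduction of new analgesic agents in the post-treatment period". The rescue medication section then classes other pain medication given during the study as rescue therapy.
- Criteria for subject withdrawal: the investigator may withdraw participants for reasons that include "adverse events, lack of compliance with the study or study procedures".

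The primary outcomes are at 3 months. Follow-up visits are at 1, 3, 6 and 12 months.

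**The concern.** In a non-inferiority trial, participants who do not receive their allocated treatment, or who receive the other one, tend to pull the ITT difference towards zero and so favour the claim. The per-protocol analysis is there as a check on that. It can do so only if the plan says that it counts, and if membership depends on treatment received rather than on something that follows from the result.

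Here one sentence includes the per-protocol analysis and a later one appears to leave it out. If the two analyses disagreed, the team could cite the text for either. The stated membership rule also leaves open three things that matter for a single procedure performed by an unblinded operator: whether a conversion to the other technique is an exclusion, which visits must be present, and whether behaviour after the procedure counts against a participant.

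**Working it through.** **1. The two sentences side by side.** The first paragraph commits to performing and reporting two analyses. The second assigns one strategy to every analysis, just before the pain comparison on which the non-inferiority claim rests. Neither paragraph names the set that supports the claim or says what follows if the results differ.

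**2. The per-protocol rule, condition by condition.**

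- *Data at the outcome time points.* The plural has no qualifier. Read per analysis, the 3-month comparison needs only a 3-month score. Read literally, it needs every visit, so a missed month 12 removes a valid 3-month score. The missing-data rule in the same section works across a participant's data, carrying values forward "approach if at least 80% of the outcome data is available for the participant". A visit-by-visit reading therefore cannot be taken for granted.
- *Adherence.* No criterion is given. Performing the assigned technique is part of the protocol, so the general wording can cover it, but receipt of that technique is not named. The not-reassigned rule covers participants who received no trial intervention. No section says how someone treated with the other technique is classified.
- *Analgesics.* New agents are advised against, and other pain medication is classed as rescue. No section makes either one a ground for exclusion.

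**3. The plan's own figure.** Inputs from Sample size: margin 1 point, SD 1.7, 80% power, alpha 0.05. The non-inferiority formula with a true difference of 0 gives 36 per arm at one-sided 0.05, which is the stated 72 in total. Then 72 / 0.9 = 80, the stated recruitment. At two-sided 0.05, the level named in the text, the result is 46 per arm. That mismatch is a separate matter; because of it, both levels are shown below.

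**4. What outcome-related exclusion could do.** Everything in this step except n and SD is assumed. Suppose a share q of an arm is excluded and those participants score g points worse than the rest. Then

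full-arm mean = mean of those kept + q × g,

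so exclusion lowers that arm's mean by q × g. The end-on minus parallel difference shrinks by g × (q_end-on − q_parallel).

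Take g = 2, a true difference equal to the 1-point margin, and SE = 1.7 × √(2/36) = 0.401. The false non-inferiority rate (noncentral t, 70 df, loss of n ignored) is:

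| q parallel | q end-on | Shrinkage (points) | One-sided 0.025 | One-sided 0.05 |
|---|---|---|---|---|
| 10% | 10% | 2 × 0.00 = 0 | 2.5% | 5.0% |
| 10% | 15% | 2 × 0.05 = 0.1 | 4.3% | 8.1% |
| 10% | 20% | 2 × 0.10 = 0.2 | 7.1% | 12.5% |
| 10% | 25% | 2 × 0.15 = 0.3 | 11.1% | 18.3% |

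In the last row, allowing for the lost participants (about 32 and 27 of 36 remain) gives 9.7% and 16.4%.

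**5. What unrecognised conversion could do.** If a share s of the end-on arm received the parallel technique but stayed in the end-on arm, a 1-point true difference would shrink by s × 1. That is 0.05 points for each 5% converted. No conversion rate is documented.

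**The case against.** The strongest reply is that adhering to the protocol naturally includes receiving the assigned technique, so a converted participant would already leave the per-protocol set. Plural time points can simply reflect several outcomes, each with its own visits. A deviation list and the handling of conversions are normally left to a statistical analysis plan, and this is a condensed article. Nor is the sentence on ITT for all analyses fatal, since the commitment to report both analyses remains in the text.

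Much of that stands. A reader might infer that the per-protocol rule drops treatment failures. The text does not support this: a participant with a poor result who attends and reports a score stays in unless analgesic use or withdrawal is counted as non-adherence, and the plan does not say that it is. A reader might also infer that the set is defined by behaviour after the procedure and keeps technique switches. That rests on silence. Nor is the per-protocol analysis denied a role; its role is contradicted. The rates in the working come from assumed imbalances and concern the per-protocol analysis alone. Exclusions for analgesic use would not touch ITT.

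The reply does not remove the conflict between two printed sentences, which a separate plan could settle but which this text leaves open. Nor does it change the fact that the article chose to state a per-protocol rule, and that the rule as stated omits the criterion most relevant to comparing two techniques.

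**Conclusion.** The point holds in limited form. The contradiction is firm and needs no assumption: the text does not fix whether ITT alone or both analyses must support non-inferiority. The per-protocol definition is ambiguous on technique received and on required visits, and one available reading selects on events after the 3-month endpoint.

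The documents do not establish any actual bias. The calculation shows only direction and possible scale: no change when the arms are shifted equally, and 4.3% to 11.1% against a nominal 2.5% for shrinkage of 0.1 to 0.3 points. It assumes a 2-point gap and more exclusions from a truly worse end-on arm. No single figure from that range should be quoted as the expected error. This should be corrected before unblinding, while the choice of set cannot be influenced by results.

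**What to change.** - Delete the sentence on ITT for all analyses, or limit it to the secondary analyses it was meant for.
- Define the 3-month per-protocol set as eligible participants who completed the allocated technique at all planned levels and have a 3-month pain score. State that analgesic use and missed later visits are not grounds for exclusion from it.
- Record on the procedure form the technique actually used, including any conversion. The article's list of intervention data does not show this item, though the full form may.
- State that non-inferiority is claimed only if the ITT and per-protocol analyses agree.

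The cost is a few lines of text and one form entry. The downside is that two analyses must succeed, so the claim is slightly harder to reach. With 80 recruited, a 10% loss leaves 36 per arm and 80.3% power at one-sided 0.05. A 20% loss from the per-protocol set leaves 32 per arm and 76.1%.

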### Hypotheses

The primary hypotheses for this non-inferiority trial are that end-on lesioning for RFN of the CMBN is non-inferior to the parallel conventional technique for its impact on the intensity of pain relief and the proportion of patients with a positive analgesic response at 3 months after the intervention in patients with chronic, moderate-to-severe neck pain in the context of cervical zygapophyseal joint syndrome. The secondary hypotheses are that end-on lesioning for RFN of the CMBN is non-inferior to the parallel conventional technique for its impact function, quality of life, sleep, adverse effects of the interventions, analgesic intake at specified time points within 1 to 12 months after the interventions in patients with chronic, moderate-to-severe neck pain in the context of cervical zygapophyseal joint syndrome.

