#### Modifications

The study participants have the right to withdraw from the study at any time. Any withdrawals will be documented along with the reason provided by the participant. If the reason for removal of a subject from the study is an adverse effect, the principal specific event will be recorded in the case report form. The subject will be followed until the adverse effect is resolved, if agreed by the subject.

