The following are the *secondary outcomes*:Pain intensity: The between-group difference in mean NRS for pain intensity scores at 1, 6, and 12 months after the interventions.Incidence of analgesic response: The between-group difference in the proportion of patients with a positive analgesic response (defined as 50% or greater reduction in the NRS score for neck pain as compared to baseline) at 1, 6, and 12 months after the interventions.Neck pain-related disability: The between-group difference in the proportion of patients with a 10% or greater reduction in the Neck Disability Index (NDI) score at 1, 3, 6, and 12 months after the interventions.Participant-assessed improvement: The between-group difference in the proportion of participants reporting some or much improvement on the Patients’ Global Impression of Change (PGIC) scale at 1, 3, 6, and 12 months after the interventions.Quality of sleep and life: The between-group difference in the mean Pittsburgh Sleep Quality Index (PSQI) scores and EuroQol (EQ-5D-5L) scores at 1, 3, 6, and 12 months after the interventions. Sleep health will be assessed using PSQI, and actigraphy-measured variables respectively, including sleep duration, sleep quality, daytime sleepiness, sleep timing, and wakefulness after sleep onset.Procedure-related outcomes: The between-group difference in the duration of procedure, discomfort, radiation dose, and cost of the procedures.Actigraphy-collected physical activity and sleep: The between-group difference in the average physical activity and sleep duration as measured by wrist-worn actigraphy over 1 week prior to the procedure and 1 week prior to the 1-month follow-up after the interventions.Adverse effects of the interventions: The between-group difference in the incidence of peri-procedural complications and post-procedural adverse effects at 1, 3, 6, and 12 months after the interventions.Analgesic requirements: The between-group difference in opioid requirements as measured by daily oral morphine equivalents in milligrams averaged over the 1 week prior to the 1, 3, 6, and 12 months follow-ups after the interventions.The patient assumption of the group they were assigned to at 3-month follow-up after the study interventions

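### Neither the allocated-arm nor the per-protocol set suits the harms comparison: one keeps untreated participants, the other drops some treated ones (small effect, cheap to fix)

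*Protocol article*

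**What the plan says.** The Statistical methods section of the protocol article names two analysis sets, both to be performed and reported:

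- The first is "intention-to-treat (based on study arm allocation").
- The second is "per-protocol (based on the participants who adhered to the study protocol and provided data at study outcome time points").

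The next paragraph of that section adds: "An intention-to-treat strategy will be used for all analyses". It makes no separate provision for harms.

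Harms are a compared outcome. The Outcomes section lists "The between-group difference in the incidence of peri-procedural complications and post-procedural adverse effects at 1, 3, 6, and 12 months after the interventions". The secondary hypothesis in the Hypotheses section is that end-on lesioning is "non-inferior to the parallel conventional technique for its impact function, quality of life, sleep, adverse effects of the interventions, analgesic intake".

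The article expects that some randomised participants may not be treated. Post-procedural management says: "In the event a subject is randomized but does not receive the trial interventions, the treatment will not be reassigned". It continues: "Trial personnel will assess the patient and collect data throughout their enrollment in the trial".

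**The concern.** Someone who had no radiofrequency procedure cannot have a complication or adverse effect of it. Under the allocated-arm rule that person still counts in the denominator, so the observed harm rate falls below the rate among people who were treated. If this happens equally in both arms, the absolute difference shrinks. For a superiority question on efficacy that is conservative. For a hypothesis of non-inferiority on harm it is not, because a true excess of harm with the new technique would look smaller.

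The per-protocol set does not supply what is missing. It excludes the untreated, but it also excludes treated people who departed from the protocol or have no data at the outcome visits. Their harms are then counted nowhere in that analysis, although they belong in a safety summary.

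The Sample size section gives a possibly lower incidence of adverse effects as one reason for a non-inferiority design. Readers will therefore want the harm rate of each technique as performed, and neither set gives it in all treated participants.

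**Working it through.** The article states no figure for the harms analysis, so there is none to reproduce. The arm size follows from the Sample size section: 72 / (1 − 0.10) = 80 recruited, and 80 / 2 = 40 per arm.

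**Inputs**
- n = 40 per arm, from the article.
- Background rate of temporary dysesthesia 43% to 67%, from Background and rationale.
- True harm difference of 20 percentage points, for example 55% v 35%: an assumption.
- Untreated participants per arm, 0 to 4: an assumption. The article gives no rate.

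**Allocated-arm set, balanced non-receipt.** Let p₁ and p₂ be the harm rates after the two techniques and u the untreated share in each arm. Untreated people contribute no procedural harm, so each observed rate is (1 − u) × p and

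observed difference = (1 − u) × (p₁ − p₂).

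| Untreated per arm | u | Observed difference (true 20) |
|---|---|---|
| 0 | 0 | 20.0 |
| 1 | 0.025 | 0.975 × 20 = 19.5 |
| 2 | 0.05 | 0.95 × 20 = 19.0 |
| 4 | 0.10 | 0.90 × 20 = 18.0 |

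The formula depends only on the difference, so the result is the same whichever technique is worse and at any base rate. If the two ends of the dysesthesia range are taken as the two rates (true difference 24.0 points), the results are 23.4, 22.8 and 21.6 for 1, 2 and 4 untreated per arm.

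The section also mentions odds ratios. At 55% v 35% the true odds ratio is (0.55/0.45) / (0.35/0.65) = 2.27. With one untreated per arm it is (0.53625/0.46375) / (0.34125/0.65875) = 2.23. The risk ratio does not change when non-receipt is balanced, because (1 − u) cancels.

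**Unbalanced non-receipt.** With 55% after parallel and 35% after end-on:
- one untreated in the parallel arm only: 0.975 × 55 − 35 = 18.6 points;
- one untreated in the end-on arm only: 55 − 0.975 × 35 = 20.9 points.

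The distortion can therefore go either way. Only the balanced case always shrinks the difference.

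**Per-protocol set.** Suppose all 40 in an arm are treated and 55% have a harm, which is 22 people. Suppose the presumed 10% dropout (4 people) lack outcome data and are excluded. If all 4 had a harm, the per-protocol rate is (22 − 4)/36 = 50.0%. If none did, it is 22/36 = 61.1%. These are the extremes. If exclusion is unrelated to harm, the expected rate stays at 55% and only numbers are lost.

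**Scale.** At 55% v 35% with 40 per arm, the standard error of the difference is √(0.55×0.45/40 + 0.35×0.65/40) = 10.9 points, so the 95% half-width is 1.96 × 10.9 = 21.4 points. A shift of 0.5 to 2.0 points is about 2% to 9% of that half-width.

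**The case against.** The strongest reply is that the intention-to-treat sentence is loosely worded and should not be read literally. The same section promises a per-protocol analysis, so allocation is not the only basis, and for untreated people exclusion is exactly the correction wanted. That stands as far as it goes. It does not help treated participants who deviated or lack data, whom the per-protocol set drops too.

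A second reply is that a journal article may leave the harms population to a statistical analysis plan. An article silent on the matter would raise no point. This one states a rule for all analyses, and an analysis plan that used a treated population would have to depart from it.

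Third, the harms outcome is worded as occurring after the interventions, and the assessment schedule records complications immediately after the procedure. This could imply that only treated people count. The reading is possible, but nothing in the article says so, while untreated participants are explicitly kept under observation.

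Fourth, the effect is small and no margin for harms is given, so the bias bears on no stated decision rule. Both parts stand. Trial design puts randomisation on the day of the procedure, which should keep non-receipt rare, although the randomisation section says it happens upon enrolment, which would leave more time for it.

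A reader might infer more: that the plan allows only allocated-arm results for harms, or that it will credit harms to a technique the participant did not receive. The documents do not support the first, because of the per-protocol commitment. The second needs participants to switch technique. No section describes switching, and Blinding mechanism has an experienced operator use the assigned technique. The abstract calls the parallel technique technically challenging, so a conversion is conceivable, but it remains only a possibility.

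Nor should a reader infer that participants who withdraw because of a harm disappear from the allocated-arm analysis. For these, "the principal specific event will be recorded in the case report form", and they are followed to resolution if they agree. Any such loss is confined to the per-protocol set.

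**Conclusion.** The point holds as a minor one. The two stated sets leave no analysis of harms in all treated participants: allocation keeps people who had no procedure, and per-protocol loses some who did. Balanced non-receipt shrinks the absolute difference by 2.5% of its value per untreated participant per arm of 40, which is 0.5 points on an assumed 20. That leans towards non-inferiority on adverse effects if end-on is in truth the more harmful technique. Unbalanced non-receipt can push either way.

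The size rests on assumed rates of harm and non-receipt that the article does not give. Within the range tried, it is well below the sampling error of the comparison. The case for change is that the harms analysis should describe the techniques as performed, and that the change costs little. It does not rest on a large expected bias or on any evidence of switching.

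**What to change.** In Statistical methods, limit the intention-to-treat sentence to efficacy outcomes and add wording such as:

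> Peri-procedural complications and post-procedural adverse effects are analysed primarily in all participants in whom a procedure was begun, grouped by the technique used. If a procedure is converted, the participant is grouped by the technique first attempted, and conversions are listed. The analysis by allocated arm is reported as a sensitivity analysis.

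The first-attempted rule keeps harm from a failed attempt with the technique that was attempted. It does nothing if no conversion occurs.

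The cost is one or two sentences and one entry on the procedure record for the technique first attempted and any conversion. No extra participants or visits are needed. The small downside is that the main harms comparison is no longer strictly by randomised group, and the allocated-arm sensitivity analysis covers that. The change should be made before the outcome data are analysed.

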### Outcomes

Patients will be assessed at baseline and 1, 3, 6, and 12 months after the study interventions. The assessment schedule and parameters are summarized in Table 2.

**Table 2 Tab2:** EndPaRL assessment schedule

**Outcome**	**Measure**	**Baseline**	**Immediate after procedure**	**1 month after procedure**	**3 months after procedure**	**6 months after procedure**	**12 months after procedure**
**Patient demographics**		**X**					
**Pain intensity**	NRS	**X**	**X**	**X**	**X**	**X**	**X**
**Neck disability**	NDI	**X**	**X**	**X**	**X**	**X**	**X**
**Global improvement**	PGIC			**X**	**X**	**X**	**X**
**Sleep quality**	PSQI	**X**		**X**	**X**	**X**	**X**
**Sleep duration**	In hours and minutes from actigraphy device	**X**		**X**			
**Physical functioning**	Time spent at different activity levels from actigraphy device^b^	**X**		**X**			
**Opioid intake**	Daily OME in mg	**X**		**X**	**X**	**X**	**X**
**Analgesics**	Name and dose	**X**		**X**	**X**	**X**	**X**
**Procedure** **(1) Duration** **(2) Cost** **(3) Discomfort** **(4) Radiation**	(1) In minute (2) In CAD (3) 0–10 (4) Dose in mSv		**X** **X** **X** **X**				
**Complications**	e.g., bleeding, hematoma		**X**				
**Adverse effects**				**X**	**X**	**X**	**X**
**Health-related quality of life**	EQ-5D-5L^a^	**X**		**X**	**X**	**X**	**X**

*CAD* Canadian dollars, *NRS* Numerical Rating Scale, *OME* Oral morphine equivalents

^a^EuroQol 5-level EQ-5D version (EQ-5D-5L); Neck Disability Index (NDI); Numerical Rating Scale (NRS); Patients’ Global Impression of Change (PGIC); Pittsburgh Sleep Quality Index (PSQI)

^b^Data on physical activity and sleep collected using participant-worn actigraphy devices (light/moderate/severe)

The following are the *primary outcomes*:The between-group difference in mean NRS for pain intensity scores at 3 months after the interventions.The between-group difference in the proportion of patients with a positive analgesic response (defined as 50% or greater reduction in the NRS score for neck pain as compared to baseline) at 3 months after the interventions.

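### The responder primary and most other dichotomous outcomes are defined as differences in proportions or incidence, but the planned effect and 95% interval are on the odds-ratio scale, so non-inferiority on the responder proportion has no planned interval on its own scale

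*Protocol article*

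**What the plan says.** The Outcomes section of the protocol article gives the second primary outcome, at 3 months, as "The between-group difference in the proportion of patients with a positive analgesic response". The same form is used for analgesic response at 1, 6 and 12 months and for two further secondary outcomes: "The between-group difference in the proportion of patients with a 10% or greater reduction in the Neck Disability Index (NDI) score" and "The between-group difference in the proportion of participants reporting some or much improvement on the Patients’ Global Impression of Change (PGIC) scale". Harms are given as "The between-group difference in the incidence of peri-procedural complications and post-procedural adverse effects at 1, 3, 6, and 12 months".

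The Hypotheses section makes the responder proportion at 3 months one of the two quantities on which end-on lesioning is to be shown non-inferior.

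Statistical methods tests categorical outcomes with chi-square and lists proportions among the descriptive statistics. It then says that treatment effects and their 95% confidence intervals "will be calculated using chi-square and odds ratios for dichotomous variables". It adds: "A set of logistic regression models for categorical outcome at 3 months will be created". No confidence interval for a difference in proportions is named.

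**The concern.** Non-inferiority is judged from a confidence interval, so the scale of the interval is the scale of the conclusion. The outcome asks how many percentage points of response, if any, are lost with the end-on technique. An interval for an odds ratio does not answer that without a further assumption about the control response rate, and a chi-square p-value does not answer it at all.

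For uncommon harms there is a second, practical problem. With about 36 patients per arm, an arm with no events is quite possible. The sample odds ratio then has no usual (Wald) interval, whereas a difference in incidence still has a finite estimate and a score-type interval.

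**Working it through.** **Inputs.** 36 per arm, or 40 per arm if all recruited patients contribute (Sample size). Literature success rates of 26% to 68%, dysesthesia 43–67% and numbness 36–58% (Background and rationale). Complication rates are assumed, because the article gives none.

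**The plan's own figure.** The article gives no calculation for a dichotomous outcome. Its 72 is for mean NRS: 2 × (1.645 + 0.842)² × 1.7² / 1² = 35.7, so 36 per arm, and 72 / 0.9 = 80. This uses one-sided 0.05. The stated two-sided 0.05 gives 46 per arm, which is a separate matter. Only the 36 and 40 per arm are used below.

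**Step 1: outcome against analysis.**

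| Outcome | Scale in Outcomes | Effect and interval in Statistical methods |
|---|---|---|
| Responders, 3 months (primary) | difference in proportions | odds ratio |
| Responders, 1, 6, 12 months | difference in proportions | odds ratio |
| NDI, PGIC | difference in proportions | odds ratio |
| Complications, adverse effects | difference in incidence | odds ratio |
| Participant's guess of allocation | not stated as a difference | odds ratio |

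The sentence on effects and intervals refers to scores for pain and for the secondary outcomes. The natural reading includes pain response. If it did not, the responder primary would be left with a chi-square p-value and no interval at all.

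**Step 2: one table on two scales.** Take 17/36 with end-on and 21/36 with parallel (illustrative).
- Difference: 17/36 − 21/36 = −0.111. SE = √[(17×19 + 21×15)/36³] = 0.117. 95% CI −34.0 to 11.8 points.
- Odds ratio: (17×15)/(19×21) = 0.64. SE of the log = √(1/17 + 1/19 + 1/21 + 1/15) = 0.475. 95% CI 0.25 to 1.62.

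Both can be estimated. Only the first is on the scale of the stated outcome.

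**Step 3: translating an odds ratio.** With control rate p0, p1 = OR·p0 / (1 − p0 + OR·p0). For an illustrative OR of 0.5 the loss is 11.1 points at p0 = 26%, 16.1 at 46%, 17.1 at 57%, 16.5 at 68% and 13.3 at 80%. The translation depends on p0, but only mildly from 46% to 80%.

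**Step 4: empty cells.** With a common rate p and n per arm, the chance that at least one arm has no events or only events is 1 − [1 − (1−p)ⁿ − pⁿ]². At p = 3% and n = 36: 0.97³⁶ = 0.334, so 1 − 0.666² = 0.556.

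| Rate | 36 per arm | 40 per arm |
|---|---|---|
| 1% (assumed) | 91% | 89% |
| 2% (assumed) | 73% | 69% |
| 3% (assumed) | 56% | 50% |
| 5% (assumed) | 29% | 24% |
| 10% (assumed) | 5% | 3% |
| 36–67% (numbness, dysesthesia) | about 0 | about 0 |

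If one arm is empty, the sample odds ratio is 0 or infinite. It is undefined only if both arms are empty in the same way: at 2%, 0.98⁷² = 23%; at 3%, 0.97⁷² = 11%.

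**Step 5: the same tables as differences.** Newcombe 95% intervals at 36 per arm: 0/36 v 3/36 gives −8.3 points (−21.8 to 2.7); 0/36 v 0/36 gives 0 (−9.6 to 9.6).

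**The case against.** Several arguments on the other side have force.

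- *The difference is not lost.* Proportions are reported, so anyone can subtract them and, from the counts, compute an interval. That stands against a claim that the stated outcome is not estimated. It does not supply a planned interval for a primary non-inferiority hypothesis.
- *It is loose wording.* The Objectives speak only of comparing proportions, and Statistical methods itself treats odds ratios as one way to express differences in treatment effects. This is possible, but a reader of the Outcomes section would expect a difference in proportions.
- *Interval methods and empty-cell handling belong in an analysis plan.* True of those details. Here, though, a scale is stated, and it is not the scale of the stated outcomes.
- *The scales nearly agree.* For an odds ratio of 0.5 the loss stays between about 13 and 17 points over control rates of 46% to 80%. The article's lower success rates are for stricter definitions at 6 and 12 months, not a 50% reduction at 3 months. So the translation problem should not be oversold.

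A reader might also infer stronger points that the article does not support:

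- That every dichotomous outcome is affected. The participant's guess of allocation is not defined as a difference.
- That the harm comparisons in general will often have no estimate. At the quoted dysesthesia and numbness rates, empty cells practically never occur. The quoted 95–100% for post-procedural pain is a literature figure that the trial does not define as a dichotomous endpoint. Procedural discomfort is scored 0–10.
- That an odds ratio is undefined whenever one arm is empty. It is 0 or infinite, and exact or corrected intervals exist, although none is named.
- That the adjusted treatment effect will be an odds ratio. The logistic models are listed, but not said to provide the treatment effect.

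**Conclusion.** The point holds as a mismatch between stated outcome and stated analysis. For the responder primary, the secondary responder, NDI and PGIC outcomes and the harms, the article defines a difference in proportions or incidence, but it plans the effect and 95% interval as an odds ratio. The consequence is greatest for the responder primary, where non-inferiority on the proportion would have no planned interval on its own scale. This rests on reading the sentence on effects and intervals as covering pain response.

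The loss of a usable odds ratio is confined to rare complications. At an assumed rate of about 3% or lower, with 36 per arm and equal rates in both arms, at least one empty cell occurs in more than half of trials. The point concerns the effect scale only. It does not depend on whether a responder margin is set.

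**What to change.** In Statistical methods, name the risk difference (end-on minus parallel) with a 95% score interval, Miettinen-Nurminen or Newcombe, as the main effect measure for the responder primary and for the other outcomes defined as differences in proportion or incidence. Keep the odds ratio as supportive. If a logistic model is used to estimate the treatment effect, also report the standardised risk difference from it, because a covariate-adjusted odds ratio differs from the unadjusted one even without confounding.

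The cost is a sentence or two of wording and slight extra programming. No new data or patients are needed.
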